# Implementation of the patient version of the evidence-based (S3) guideline for psychosocial interventions for patients with severe mental illness (IMPPETUS): study protocol for a cluster randomised controlled trial

**DOI:** 10.1186/s13063-020-4200-z

**Published:** 2020-03-18

**Keywords:** Guideline, Implementation, Patient version, Cluster randomised controlled trial

## Abstract

**Background:**

The German guideline on psychosocial interventions for people with severe mental disorders recommends a broad spectrum of evidence-based treatments. Structured implementation of the associated patient version of the guideline is missing to date. The study aims to assess whether structured implementation of a patient guideline improves the empowerment of patients with severe mental disorders, as well as knowledge, attitudes and experiences regarding psychosocial interventions, service use, treatment satisfaction, treatment needs, quality of life and burden of care.

**Methods:**

The study is a multicentre, cluster-randomised, controlled study with two parallel groups. Inpatients and day hospital patients (all sexes; 18–65 years) with severe mental disorders will be included. Additionally, relatives of patients with mental disorders (all sexes; ≥ 18 years) will be included. In the experimental group, the patient guideline will be implemented using a multimodal strategy. Participants in the control group will receive treatment as usual but will be made aware of the patient guideline. The primary outcome is the change of empowerment, assessed by using the ‘empowerment in the process of psychiatric treatment of patients with affective and schizophrenia disorders’ (EPAS) scale. In addition, knowledge, attitudes and experiences regarding psychosocial interventions will be assessed as secondary outcomes, as well as service use, satisfaction with care, patient need and quality of life and participation and social inclusion. For relatives, the perceived burden of care also will be recorded. Results will be analysed using hierarchical linear models. For the health economic evaluation, the incremental cost-utility ratios will be computed using the differences in total costs of illness and the differences in quality-adjusted life years (QALY) between study groups.

**Discussion:**

The study will be the first to assess the effects of a structured implementation of the patient version of a psychiatric treatment guideline. The study has some limitations regarding the transferability of the results to other patients and other regions. Furthermore, problems with the recruitment of patients and relatives and with the implementation of intervention could occur during the study.

**Trial registration:**

The study is registered in the German Clinical Trials Register (DRKS) and the WHO International Clinical Trials Registry Platform (ICTRP) under registration number DRKS00017577 (Date of registration: 23 October 2019.

## Background

Psychosocial interventions aim to improve the ability of individuals to live in their social environment and participate in society [1]. They are a core component in the treatment of persons with severe mental illness. A wide range of very different psychosocial interventions exist, e.g., occupational therapy, art therapy and supported employment [1]. In 2012 the first version of the evidence- and consensus-based (S3) guideline ‘Psychosocial interventions in severe mental disorders’ of the German Association for Psychiatry, Psychotherapy and Psychosomatics (DGPPN) was published and provided a comprehensive assessment and appreciation of the available evidence on the efficacy of psychosocial interventions for persons with severe mental illness [1]. In addition, an associated patient guideline that reproduces the recommendations in plain language has been prepared to promote active participation of the patients in their treatment [2]. Both versions of the guideline were updated in 2019 [1, 2]. However, evidence suggests that patients in Germany are informed insufficiently about these interventions and that utilization rates are low [3]. Furthermore, at least in Germany, the uptake of psychosocial interventions seems to depend more on regional structures than on evidence [4].

While the pathway of evidence synthesis and guideline development is sophisticated, evidence on the effects of implementing treatment guidelines for mental illness in clinical practice is sparse and inconsistent [5]. In particular, the effects of patient guidelines have not been studied rigorously. Currently, no controlled study exists that has put to test whether an implementation of a psychiatric patient guideline has an influence on treatment utilization or outcomes. Some encouraging evidence of positive effects of patient information or patient guidelines can be derived from studies using, e.g., patient brochures in guideline implementation [6].

The present project aims to shed light on the effects of a structured patient guideline implementation within a multicentre, cluster-randomised, controlled, non-blinded, superiority study with a 1:1 allocation.

### Objectives

#### Primary objective

The primary objective is to assess, while using the ‘empowerment in the process of psychiatric treatment of patients with affective and schizophrenia disorders (EPAS)’ scale, whether a structured implementation of the patient guideline ‘Psychosocial interventions in severe mental disorders’ improves the empowerment of patients with severe mental disorders with regard to their treatment.

#### Other objectives

In addition, whether the structured implementation of the patient guideline ‘Psychosocial interventions in severe mental disorders’ is able to achieve the following is also assessed:
improve knowledge, attitudes and experiences of the patients and relatives about available treatmentsimprove service use by patients with severe mental disordersimprove treatment satisfaction of patients with severe mental disorders and their relativeschange treatment needs and coverage of needs of patients with severe mental disordersimproved quality of life of patients with severe mental disorders and their relativescause the gain of one quality-adjusted life year (QALY) in comparison to treatment as usual (TAU) at a maximum willingness to pay (MWTP) threshold of between 0 and 100.000 €reduce the burden of care of relatives of patients with severe mental illness

## Methods/Design

This protocol describes a cluster-randomised controlled study, which is the second part of a larger project that also includes a cross-sectional study in the first part [7]. In the first part, an assessment of the current status of the implementation of the S3 guideline recommendations for psychosocial interventions was conducted. Furthermore, this cluster-randomised controlled study will be supplemented by a separate qualitative study.

The protocol was prepared in accordance with the SPIRIT statement (*see* Additional file 1) [8].

### Study design and setting

The study is a multicentre, cluster-randomised, controlled, non-blinded, superiority study with two parallel groups. Randomisation will be performed as a stratified block randomisation [9] with a 1:1 allocation (*see* ‘Randomisation’ section). Data will be collected in 10 clinics for psychiatry and psychotherapy, which provide in- and outpatient psychiatric care to the inhabitants of Upper Bavaria and Swabia, Germany. The centres provide care for metropolitan catchment areas (Augsburg and Munich), middle-urban regions (Kempten and Memmingen) and rural regions (Donauwörth, Günzburg, Kaufbeuren, and Taufkirchen).

### Eligibility criteria

Inpatients and day hospital patients will be included if they have a severe mental disorder according to the definition of the S3 guideline ‘Psychosocial interventions in severe mental disorders’ (disease duration of ≥ 2 years and substantial impact on activities of daily life) [1]. However, in contrast to the S3 guideline, the inclusion criteria for the present study will be limited to patients with schizophrenia, schizotypal and delusional disorders (ICD-10 F2x) or mood [affective] disorders (ICD-10 F3x) to obtain a more homogenous sample [10]. Considerable consequences on the activities of daily life will be defined as a ‘Global Assessment of Functioning’ (GAF) [11] score ≤ 60 and a ‘Health of the Nation Outcome Scales’ (HoNOS) [12] fulfilling one of two conditions: (a) a score of ≥ 2 on one of the items of the subscale for symptomatic problems (items 6, 7 and 8) and a score of ≥ 2 on each of the four items of the subscale for social problems (items 9, 10, 11 and 12) or (b) a score of ≥ 3 on at least one of these items (9, 10, 11 or 12). Patients of all sexes will be included if they are between the ages of 18 and 65 years. Patients need to have sufficient capacity to understand the research project and to decide about their participation. In case of doubts about the ability to obtain consent of the patient, the responsible physician will decide on the capacity to consent. Legal representatives of patients (if available) will be informed about the study participation in case of consent from the patient.

To include the perspective of relatives of patients with mental disorders, relatives of all sexes will be included if they are aged over 18 years and if they are capable of understanding the research project. Relatives will only be included if they are not in current inpatient or day hospital mental health care.

### Recruitment procedure

The recruitment and data collection will be conducted from October 2019 to March 2021. Eligible patients will be approached and informed about the IMPPETUS study by the study staff to determine whether they would be willing to participate in the study, especially giving the consent to be willing to participate at a time point 6 months after intervention (t_2_). If the patients give their consent, a screening with the ‘Global Assessment of Functioning’ (GAF) and the ‘Health of the Nation Outcome Scales’ (HoNOS) will be carried out to identify patients with severe mental illness according to the definition above. The screening will be conducted as soon as possible after admission. For more details *see* Fig. 1.

**Fig. 1 Fig1:**
[figure not shown]
Flow of participants

Relatives will be addressed by the study staff in relatives groups and made aware by posters/flyers at the hospitals.

### Interventions

In centres randomised to the experimental group, the patient guideline ‘psychosocial interventions in severe mental disorders’ will be implemented using a multimodal strategy. The core component will be a two-part group session for patients of more than 60-min duration in which the contents of the patient guideline will be clearly presented (e.g., with case examples). The group session will be carried out jointly by the study staff (e.g., a psychologist) and a peer tutor (person with a lived experience of mental illness). The group sessions will also pay attention to the availability of psychosocial interventions in the regions but will not be limited to regional offers. In addition, questionnaires and decision aids on the basis of the patient guideline will be developed to assist patients in their discussions with practitioners and to promote their active demand for suitable psychosocial therapies. Training for the use of the questionnaires and decision aids will be provided in group sessions. Individual reminders will be developed. The two-part group sessions will be offered weekly in the inpatient and day hospital setting. Participation in both parts of the event will be supported by written information flyers. Repeated participation is possible, but study participants should attend both parts at least once. Furthermore, participants will receive the patient guideline as a printed book. Essential contents of the patient guideline will be made available on the Internet and will be optimized for mobile use (www.thera-part.de). The group sessions will include a brief introduction on how to use ‘TheraPart’. The plain language materials will be developed or tested with the participation of representatives of patients and relatives. A on-part information event for relatives will occur parallel to the two-part group events for the patients.

Patients in centres randomised to the control condition will receive treatment as usual but will be made aware of the patient guideline ‘Psychosocial interventions in severe mental disorders’ by receiving the same guideline flyers as participants in the intervention group, which summarises the key information of the guideline and refers to additional sources of information. Treatment as usual (TAU) was chosen as the control group to compare the intervention with standard treatment. Participating relatives of patients in clinics randomised to the control condition will also receive the flyer for the guideline.

Prior to the start of the study, all study staff will receive comprehensive training on the implementation of the assigned study conditions to ensure a consistent procedure across all sites. Regular retraining and supervision of the study staff will also take place. Regular exchange between all study staff and the study lead will ensure compliance with the study protocol.

### Outcomes and measurement

#### Patient-relevant outcomes and measurements

##### Primary outcome

The primary outcome is the improvement of empowerment (*see* objective 1) after 6 months, which will be measured as change according to the ‘empowerment in the process of psychiatric treatment of patients with affective and schizophrenia disorders’ (EPAS) scale [13]. The scale comprises a basic module with 33 items, which include the five dimensions ‘everyday coping‘, ‘social relationships‘, ‘treatment participation‘ and ‘hope and self-efficacy‘. Two add-on modules also cover empowerment in the care of underage children and at work. The questionnaire, whose psychometric properties have been successfully tested in a field study [13], provides a comprehensive record of empowerment in the psychiatric treatment process. Patients and their relatives will be interviewed with the EPAS.

##### Other outcomes

Changes in patient knowledge, attitudes and experiences regarding available treatments (*see* objective 2) will be assessed using a checklist developed for this study. The checklist includes all psychosocial interventions of the S3 guideline ‘psychosocial interventions’ (can be provided on request) and address the following:
Changes in service use (*see* objective 3) will be measured as changes on the German version of the ‘Client Sociodemographic and Service Receipt Inventory’ (CSSRI) [14]. The CSSRI is a semi-structured interview to assess social and demographic data, accommodation data, detailed information regarding treatment, professional visits and social and health service utilisation for estimating healthcare costs. Additionally, the CSSRI systematically records the use of psychiatric, medical, psychosocial and rehabilitative health services (direct costs) and productivity losses (indirect costs) and therefore completely covers the costs of the disease from an economic perspective. Therefore, the health economic evaluation (see objective 6) will be based on the data collected with the CSSRI. An appropriate pre-structuring of the requested health care services will ensure that the receipt of the psychosocial care services recommended in the S3 guideline ‘Psychosocial interventions’ will be assessed.Satisfaction with treatment (*see* objective 4) of the patients will be assessed with the German satisfaction questionnaire ‘ZUF-8’ [15]. The ZUF-8 has eight items and is a one-dimensional measure of satisfaction to record the general or overall patient satisfaction with the treatment received. The item values are summed. High scale values indicate a large level of satisfaction and low scale values a low ‘satisfaction‘ (range from 8 to 32).Changes in patient treatment needs and coverage of needs (*see* objective 5) will be assessed by using the German version of the ‘Camberwell Assessment of Need’ (CAN-EU) [16, 17]. The CAN-EU assesses 22 domains of potential individual care needs. Each domain is rated on a 3-point scale from the absence of need (= 0) to the presence of an unmet need (= 2). A total score is calculated by adding the domain ratings.Quality of Life (QoL; *see* objective 6) of the patients will be measured with the German version of the World Health Organization’s Quality of Life Instrument-abbreviated version (WHOQOL-BREF) [18, 19]. The WHOQOL-BREF is a tool with 26 items: 24 items in four domains: physical (seven items), psychological (six items), social (three items) and environmental (eight items), and two additional items: the overall quality of life (item 1) and level of satisfaction with health (item 2). The items are rated on a five-point Likert-type scale. To calculate domain scores, the mean of all items within a domain is multiplied by four. Subsequently, these raw domain scores are transformed into a scale from 0 to 100 points (to enable comparisons to be made between domains composed of unequal numbers of items), with higher scores denoting better QOL.The calculation of quality-adjusted life years (QALYs; *see* objective 7) will be based on the German Version of the EuroQol (EQ-5D-5 L) [20–22]. The EQ-5D-5 L generates health states at five dimensions as a basis for the generation of QALYs. The EQ-5D-5 L questionnaire includes five questions on current issues in the dimensions of ‘mobility‘, ‘self-care‘, ‘usual activities‘, ‘pain/discomfort‘ and ‘anxiety/depression‘. Five possible answers exist for each dimension: (1) no problems, (2) slight problems, (3) moderate problems, (4) severe problems and (5) unable to do. QALYs will be generated by means of the German value set [23].In addition, the participation and social inclusion of the patients will be assessed using the German questionnaire ‘Fragebogen zur Erfassung sozialer Partizipation und sozialer Inklusion chronisch psychisch erkrankter Menschen’ (F-INK) [24]. The F-INK measures the participation and social inclusion of individuals with a chronic mental disorder. It is a modular questionnaire with nine modules that assess the central dimensions of social inclusion [24].Sociodemographic data of the patients (e.g., sex, age and socioeconomic data) and patient medical history will be assessed within the CSSRI. The patient’s medical history (diagnosis, length of illness, length of current disease episode, number of previous episodes and current somatic and psychotherapeutic treatment) will be derived from the patient or the patient’s record data.

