
#### Relatives—relevant outcomes and measurements

Relevant outcomes and measurements for relatives include the following:
The mental disorder, the disorder severity and the restrictions in daily life of the participants’ mentally ill relatives will be assessed with a separate questionnaire.Changes in the relatives’ knowledge, attitudes and experiences regarding available treatments (*see* objective 2) will be evaluated using the same developed checklist that was used for patients.Satisfaction with treatment (*see* objective 4) from the perspective of the relatives will be assessed with the ZUF-8 (*see* above).Changes in treatment needs and coverage of needs of the mentally ill relatives (see objective 5) will be assessed by using the CAN-EU (*see* above).Quality of Life (QoL) of relatives of patients with severe mental illness (see objective 6) will be measured with the WHOQOL-BREF (*see* above).Relatives’ burden of care (*see* objective 8) will be assessed using the ‘Burden Assessment scale’ (BAS) [25]. The BAS is a 19-item scale that focuses on specific subjective and objective consequences of relatives caring for persons with severe mental disorders within the past 6 months. Answers are given on a 4-point Likert scale ranging from (1) not at all to (4) very much, with higher values indicating stronger burden.Sociodemographic data of the relatives will be assessed with a separate questionnaire.

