### Sample size

Sample size calculation was based on a two-step procedure due to the hierarchical data structure. In the first step, the sample size for an individual randomized study is calculated. Based on studies using the ‘empowerment in the process of psychiatric treatment of patients with affective and schizophrenia disorders (EPAS)’ scale [26], a medium effect (0.4 SD units) of the implementation intervention on the primary endpoint is expected. This effect is detectable with an error probability of 5% (alpha) and a power of 80% by a t-test for independent samples with a sample size of 2 × 100 participants (200 in total).

The second step takes the cluster structure of the data into account. We assume that each centre recruits 35 patients (m) on average. The design effect (DE) is needed for the inflation of the group sample size: DE = 1 + (m - 1) * ICC with the fixed cluster size m and the intra-cluster correlation coefficient ICC. We assume a liberal intra-class correlation coefficient of 0.02 to control for the correlation of the outcome of participants of the same centre. Thereby, the DE is 1 + (35–1) * 0.02 = 1.68, which gives a sample size of 200 × 1.68 = 336 patients. As every centre recruits 35 patients on average, 10 centres are needed for the trial. Due to the severity of the disease in the patient population, case number planning assumes that 70% of patients can be reached 6 months after t_0_, so that an oversampling to (35/0.7) 50 patients per study centre will be recruited, resulting in 10 centres * 50 patients = 500 participants (2 × 250) as the overall sample size. This 70% estimate is based on experiences at the Günzburg site from three studies conducted with similar populations [27–29].

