All other outcomes (*see* chapter ‘Outcomes and measurement’) will be analysed in a similar way. Subgroup analyses will be conducted separated by recruiting centres. Patient-related analyses (knowledge, attitudes, and experiences, service use, satisfaction with treatment, treatment needs and quality of life) will be conducted separately for patients with F2x and F3x diagnoses in additional subgroup analyses. Other categorisations based on quantitative variable are not planned.

Health economic evaluation (HEA) will be conducted from the societal and from the payer (statutory health insurance) perspective. Incremental cost-utility ratios (ICUR) will be computed using the differences in total (direct and indirect) costs of illness and the differences in quality-adjusted life years (QALY) between study groups over 12 months for the societal perspective. For the HEA from the payer perspective only the direct costs reimbursed by the statutory health insurance will be used as ICUR numerator. For both perspectives the stochastic uncertainty of the ICUR will be estimated by means of nonparametric bootstrapping with 2000 replications [34]. Probability of cost-effectiveness at MWTP for the gain of one QALY in the range between 0 and 100,000 € will be estimated for both perspectives by means of the cost-effectiveness acceptability curve [34]. The calculation of the QALY is based on the EQ-5D-5 L by means of the German value set [23].

All analyses will be conducted separately for patients and relatives.

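### The one CAN-EU score named for objective 5 mixes met and unmet needs, so a change in it cannot be attributed to fewer needs or to better-met needs

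*Protocol article*

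**What the plan says.** In the protocol article's own numbering, in which the primary objective is number 1, the needs objective under Other objectives is objective 5. It names two things: the needs themselves and their coverage.

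Under Other outcomes, "Changes in patient treatment needs and coverage of needs" are tied to objective 5 and assigned to the CAN-EU. The scoring is then set out:

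- The instrument has 22 domains.
- On how a domain is scored, the article says: "Each domain is rated on a 3-point scale from the absence of need (= 0) to the presence of an unmet need (= 2").
- On the variable derived from these scores, it says: "A total score is calculated by adding the domain ratings".

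For relatives, the section on relatives' outcomes lists "Changes in treatment needs and coverage of needs of the mentally ill relatives" with the same instrument, by reference back to the patient text. Statistical methods then says that all other outcomes "will be analysed in a similar way" to the primary one. For the primary outcome that means a hierarchical linear model of the month-6 value on intervention, baseline value, centre and centre size.

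The article names no count of met needs, no count of unmet needs and no coverage ratio. It does not label the middle rating.

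**The concern.** The objective has two targets and the only derived score has one dimension. A domain that moves from unmet to met is better coverage and lowers the total by 1. A domain that moves from no need to a met need is a newly recognised need that is being served, and it raises the total by 1. A met need that disappears lowers the total by 1, exactly as better coverage does.

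This matters for an intervention meant to inform patients about psychosocial treatments and encourage them to ask for these. Such an intervention could plausibly affect both coverage and the number of needs reported. If the total is what enters the model, a fall could be reported as better coverage when it reflects fewer needs, or the reverse. A flat total could hide a shift between met and unmet needs.

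**Working it through.** The article states no CAN-EU range, effect size or power, so there is no figure of its own to reproduce. The check is algebraic.

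**Inputs.** From Other outcomes: 22 domains, 0 = no need, 2 = unmet need, total = sum of ratings. Assumption: rating 1 = met need. This is inferred from the two labelled ends and from the objective's reference to coverage.

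**Formulas.** Let M be the number of met needs (rated 1) and U the number of unmet needs (rated 2), with M + U ≤ 22.

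- Needs present: N = M + U
- Share of needs met: C = M / (M + U)
- Total: T = M + 2U = N + U, with range 0 to 44

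The last line is the core of the point: the total is the number of needs plus the number of unmet needs, so it merges the two targets of objective 5.

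**Different states, same total.**

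| Unmet U | Met M | Needs N | Total T | Share met C |
|---|---|---|---|---|
| 4 | 4 | 8 | 2×4 + 4 = 12 | 4/8 = 50% |
| 1 | 10 | 11 | 2×1 + 10 = 12 | 10/11 = 91% |
| 6 | 0 | 6 | 2×6 + 0 = 12 | 0/6 = 0% |
| 0 | 12 | 12 | 2×0 + 12 = 12 | 12/12 = 100% |

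Enumerating every split over 22 domains, only the totals 0, 1, 43 and 44 fix M and U. Every even total from 2 to 22 can arise both with no need met (U = T/2, M = 0) and with every need met (M = T, U = 0).

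**Changes from one starting state** (M = 4, U = 3, T = 10, C = 4/7 = 57%).

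| Change | M | U | T | C |
|---|---|---|---|---|
| One need goes from unmet to met | 5 | 2 | 9 | 5/7 = 71% |
| Two go from unmet to met, two new needs arise and are met | 8 | 1 | 10 | 8/9 = 89% |
| One unmet need disappears | 4 | 2 | 8 | 4/6 = 67% |
| Two met needs disappear | 2 | 3 | 8 | 2/5 = 40% |

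Row 1 shows that the total does respond to coverage when N is constant. Row 2 shows cancellation. Rows 3 and 4 give the same fall of 2, while the share of needs met rises in one and drops in the other.

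**Illustration on assumed inputs.** The documents give no rates, so all of the following are assumptions: on average 4 met and 3 unmet needs per patient (hence 15 domains without need), domains independent, 100 patients per arm without clustering or baseline adjustment, no change in the control arm, and 20% of unmet needs becoming met under the intervention. The rate at which no-need domains become met needs is varied. The expected difference in T is −3 × 0.20 + 15 × rate. The expected difference in U is −3 × 0.20 = −0.60 throughout. The shares come from 4,000 simulated trials per row.

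| Rate of new met needs | Expected difference in T | Trials with T significant | Trials with U significant |
|---|---|---|---|
| 0% | −0.60 | 25% | 79% |
| 2% | −0.30 | 10% | 78% |
| 4% | 0.00 | 5% | 78% |
| 6% | +0.30 | 10% | 78% |

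These rows show what the score can do. They do not predict what will happen in this trial.

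**The case against.** The strongest reply is that the sentence on the total describes the instrument and does not define an endpoint. The ZUF-8 and WHOQOL-BREF entries carry similar scoring notes. The sentence that assigns the outcome names both needs and coverage, and Statistical methods never mentions a CAN-EU total. An analysis plan that is not shown may define the counts. This stands in part. The article does not say that the total is the only variable to be analysed, and leaving detail to the analysis plan is no fault. What remains is that the one score it does name does not separate the two targets it is attached to.

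A reader might go further and infer that the total cannot answer objective 5 at all. The documents do not support that: with the number of needs unchanged, each need moving from unmet to met lowers the total by 1. The weakness is attribution.

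A reader might also infer that cancellation is to be expected, so that a real benefit would be hidden. The Interventions section says that the materials should encourage patients to ask for suitable therapies. It does not say that patients will report new needs in the CAN-EU domains. Cancellation also requires the two movements to be of similar size, and no rate is given for either. The tied examples above were chosen to tie.

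Two further reservations hold. The meaning of rating 1 is inferred. The counts are small integers, so the linear mixed model should not be carried over to them without a check.

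**Conclusion.** The concern holds in a limited form. Given that rating 1 means a met need, the total equals needs present plus unmet needs. A change in it cannot be assigned to either part of objective 5, and opposite movements can cancel. The ambiguity is wide: a total of 12 is compatible with anything from no needs met to all needs met.

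The result rests on the article's scoring rule and on the reading of the middle rating. The simulated figures rest on assumed rates and carry no weight beyond illustration. Whether cancellation would occur in this trial is unknown.

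The consequence is confined to one non-primary outcome, measured in patients and in relatives. The confirmatory EPAS test and the sample size, which is built on EPAS, are unaffected. All 22 ratings are collected, so nothing is lost if the variables are named before analysis.

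**What to change.** For objective 5, name two CAN-EU variables:

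1. **Coverage:** the number of unmet needs (domains rated 2).
2. **Needs:** the number of needs present (domains rated 1 or 2).

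Adjust each for its own baseline count and keep the centre structure of the primary model. Use a model suited to counts, or check that the linear mixed model fits. Do this for patients and for relatives' ratings. Report the two results together, because unmet needs can also fall when needs disappear. State that rating 1 is a met need. Keep the summed total as a supplementary description. A share of needs met could be shown as well, but it is undefined for anyone with no needs and should not be the main coverage measure.

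**Cost.** No new data: both counts come from the same 22 ratings. In each population two count models replace one total-score model, which is one additional exploratory secondary outcome for patients and one for relatives. Any planned subgroup analyses of the needs outcome would be run on both counts.
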